# METHODS

STUDY STEPS

First step

Research sites and Study design

This step will be carried out in Brasília, Curitiba, Santa Catarina, Ribeirão Preto, Espírito Santo in the form of a pragmatic, open-label, randomized clinical trial in health units that provide care to patients with Tuberculosis and whether or not they have a Tuberculosis Control Program (PCT acronym in Portuguese). ). The health facilities that prescribe LTBI treatment will be chosen. From June 2018 to March 2019, people over 18 years of age with indication for LTBI treatment will be invited to participate in this study.

After signing the informed consent term, the contacts will be randomized to receive Isoniazid 100mg or 300mg and will be followed up until the end of treatment.

The primary outcome will be the success rate of LTBI treatment in the new 300mg formulation represented by the proportion of subjects with 270 doses of isoniazid between 9 to 12 months.

Secondary outcomes will be evaluated by comparing adverse effects in the two groups (Isoniazid 100mg or 300mg).

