LTBI treatment success and dropout rates will be calculated for each study group. Student's t test will be used to compare means and Pearson's chi-square test will be used to compare proportions and the variables associated with the outcome of interest (p < 0.20) will be included in the multivariate regression model for adjustment. Results are presented in relative risk (RR) with a 95% confidence interval (95% CI). Ideally, all subjects included in the study should complete it following the initial protocol. This situation almost never happens, for different reasons. In general, there are losses, non-adherence to treatments and other deviations from the protocol. For the analysis of the results, two basic populations will be defined: the first is defined by the “intention-to-treat” (ITT) which will include all patients regardless of protocol violations and loss to follow-up; the second, referred to as “per-protocol” (PP), will be a subset of the first, including only patients who completed treatment according to the protocol criteria, excluding all violators. These two analyzes are important, as a significant violation of the criteria established in the protocol (many losses, switching or poor adherence to treatment, and/or other deviations) in the ITT analysis may include a no-difference bias resulting in a lower treatment effect and greater risk of falsely declaring non-inferiority. On the other hand, the PP analysis, in these adverse situations, may include a difference bias, resulting in a greater effect of the treatments and a greater risk of falsely declaring superiority. Therefore, ITT analyzes are conservative for superiority while PP are conservative for non-inferiority. We will therefore present both and the CONSORT Statement will also be used throughout the report (Schulz, Altman and Moher, 2010). All analyzes will be performed in Stata, version 15.0.

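### The per-protocol set is selected on the primary outcome, so for treatment success it can only show 100% in both arms, and it is not conservative for this endpoint

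*Protocol*

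**What the plan says.** In the Protocol, METHODS (First step), the primary outcome is LTBI treatment success, "represented by the proportion of subjects with 270 doses of isoniazid between 9 to 12 months". SAMPLE SIZE CALCULATION works with its complement, abandonment: 19% expected with the 300 mg tablet and 30% with the 100 mg tablet, with 80% power to detect a difference at the 5% level.

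ANALYSIS PLAN announces that "LTBI treatment success and dropout rates will be calculated for each study group", with Pearson's chi-square for proportions and relative risks with 95% confidence intervals. It then defines two populations. ITT is the one "which will include all patients regardless of protocol violations and loss to follow-up". PP "will be a subset of the first, including only patients who completed treatment according to the protocol criteria, excluding all violators". The violations it has in mind are "many losses, switching or poor adherence to treatment, and/or other deviations". It concludes: "Therefore, ITT analyzes are conservative for superiority while PP are conservative for non-inferiority. We will therefore present both".

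**The concern.** A per-protocol analysis is useful only if people can be in the set and still fail the endpoint. Here completing treatment is the endpoint, and completing treatment is also the entry condition for PP. Losses and poor adherence, which are how a participant fails to reach 270 doses, are listed as reasons for exclusion.

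The plan promises to show PP next to ITT and tells the reader to treat PP as the cautious analysis for non-inferiority. If ITT showed no advantage, or a disadvantage, for the 300 mg tablet, the PP table would still show identical success in both arms. The protocol's own text would encourage reading that as reassurance.

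**Working it through.** **Step 1. Compare the two definitions.**
- Primary success (METHODS): 270 doses within 9 to 12 months.
- PP membership (ANALYSIS PLAN): completed treatment by the protocol criteria, with no violation.
- The only criterion the protocol states for completing trial treatment is 270 doses in 9 to 12 months. So PP membership implies primary success, and PP is the set of completers less any who are excluded for another violation such as switching.

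**Step 2. Reproduce the planned size, to get numbers per arm.**
- Inputs: abandonment 0.30 and 0.19, power 80%, 5% level (two-sided assumed).
- Per arm: (0.30×0.70 + 0.19×0.81) × 7.849 / 0.11² = 0.3639 × 7.849 / 0.0121 = 236.05, so 237.
- Both arms: 474, the protocol's figure. The text attaches it to each group, but on these inputs it is the total.
- 474 × 1.15 = 545.1, so 546, also as stated. The site quotas agree if the quota of 90 applies to the four centres other than Espírito Santo: 186 + 4×90 = 546.
- I therefore take 546 as the two-arm total, 273 per arm.

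**Step 3. Apply the planned rates to everyone (illustrative).**
- 300 mg: 0.81 × 273 = 221 successes. 100 mg: 0.70 × 273 = 191 successes.

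| Set | 300 mg | 100 mg | RR for success |
| --- | --- | --- | --- |
| ITT | 221/273 (81%) | 191/273 (70%) | 221/191 = 1.16 |
| PP as written | 221/221 (100%) | 191/191 (100%) | 1.00 |

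- ITT: SE of log RR = √(1/221 − 1/273 + 1/191 − 1/273) = 0.049, so the 95% CI is about 1.05 to 1.27.
- PP: SE = √(1/221 − 1/221 + 1/191 − 1/191) = 0, so the interval has no width. The failure column of the 2×2 table is empty, its expected counts are 0, and chi-square is undefined. The relative risk for dropout is 0/0.
- Further PP exclusions would reduce 221 and 191 but leave both proportions at 100%.

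**Step 4. Check the claim that PP is conservative for non-inferiority.** The protocol gives no margin, so the margins here are assumptions. With everyone a success, the Newcombe 95% lower bound for the difference in success is −z²/(n + z²), where n is the number of completers on 300 mg and z² = 3.84. It depends on nothing else. At 221 completers it is −3.84/224.84 = −1.7 points. With true 300 mg success of 60% (164 completers) it is −3.84/167.84 = −2.3 points. With 30% (82 completers) it is −3.84/85.84 = −4.5 points.

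I simulated 20,000 trials per scenario with 273 per arm and 70% success on 100 mg. ITT used the Wald lower bound and PP the Newcombe lower bound. With an assumed margin of 10 points:

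| True success, 300 mg | ITT meets margin | PP meets margin |
| --- | --- | --- |
| 60% (10 points worse) | 2.5% | 100% |
| 50% (20 points worse) | 0% | 100% |
| 30% (40 points worse) | 0% | 100% |

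For this endpoint, PP is the permissive analysis and ITT the strict one, the opposite of what ANALYSIS PLAN says.

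**The case against.** **No non-inferiority claim is planned.** A reader might infer that the trial would declare non-inferiority through PP whatever the truth. The documents do not support that. The protocol has no non-inferiority hypothesis, margin or test. The sample size is for a difference, and the passage on populations reads as a general justification for showing two analyses. The inference is also too strong numerically: with a 5-point margin and 300 mg truly 40 points worse, PP meets the margin in about 89% of simulated trials, and with a 2-point margin and 300 mg truly 10 points worse it almost never does (0.1%). A table of 100% against 100% would also look odd to a careful reader. This objection stands against any claim about a decision rule. It does not rescue the PP analysis or the sentence about conservatism.

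**PP is not only for completion.** A reader might infer that PP is empty for every outcome. It is not. Adverse effects are compared as a secondary outcome, and there a completers-only set may be selective but does not give a fixed answer. The point is limited to success and dropout.

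**ITT leads anyway.** The plan calls ITT conservative for superiority, and the trial is sized for superiority. One might object that neither population is named as decisive, but that is commonly settled in a statistical analysis plan, which is not shown, so it is no part of this point.

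**Completion might be meant more loosely.** The plasma sub-study places the end of treatment at the sixth month, and the knowledge questionnaire expects six to nine months. Neither is offered as a criterion for completing trial treatment. Even a looser rule would leave PP selected on a near copy of the outcome.

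**The counts rest on assumptions.** True: 273 per arm is a reading of the text, and the plan does not say how lost participants are counted. The 100% results do not depend on either.

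**Conclusion.** The point holds for treatment success and dropout. As written, PP returns 100% success and 0% dropout in both arms for any true rates, so it carries no information on the primary comparison and cannot corroborate or challenge ITT. At the planned rates, an 11-point difference (81% versus 70%) becomes zero by construction. The statement that PP is conservative for non-inferiority is reversed for this endpoint.

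This rests on one reading: that the protocol's completion criterion is its primary-outcome criterion, the only one it states. The counts 221 and 191 are illustrative, and the simulated percentages depend on assumed margins. The ITT analysis, the sample size and the randomisation are not affected. The exposure is misinterpretation of a companion analysis.

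**What to change.** In ANALYSIS PLAN:

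1. Define PP without reference to completion or number of doses. For example: participants who met the eligibility criteria, and who received and stayed on the allocated tablet strength for as long as they were on treatment. Those who abandon treatment then remain in the set and count as failures.
2. Present PP as supportive to the ITT superiority comparison. It still conditions on events after randomisation, so it should not carry the conclusion.
3. Delete the non-inferiority rationale, or state that no non-inferiority conclusion will be drawn because no margin was set.

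The cost is one reworded paragraph. Data collection, sample size and procedures do not change. The sponsor gives up only a non-inferiority reading that was never planned.

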# INTRODUCTION

The World Health Organization (WHO) defines latent Mycobacterium tuberculosis infection (LTBI) as a state of persistent immune response to stimulation by Mycobacterium tuberculosis antigens without evidence of clinical manifestations of active tuberculosis (TB). It is estimated that a quarter of the world population is infected by this bacterium. Despite the absence of symptoms, there is a risk of these patients developing active TB, especially in the first two years after the primary infection worsened in the case of immunosuppression. Activation occurs in 5-10% of cases (LEITE-JÚNIOR, 2017).

Thus, the evaluation of contacts of TB cases is of relevant importance for the screening of LTBI, which requires proper diagnosis and treatment, with the aim of preventing the development of active TB in the future, also interrupting the disease transmission cycle. In Brazil, the National Tuberculosis Control Program/Ministry of Health (PNCT) considers any person who lives in the same environment as the index case as contact at the time of diagnosis of TB. Contacts under the age of five, people with HIV and people with high-risk conditions should be considered a priority in the process of evaluating contacts and treating LTBI (BRASIL, 2017).

The drug Isoniazid is used worldwide for the treatment of LTBI and reduces the risk of illness by 60 to 90%, depending on adherence and duration of treatment (WHO, 2015). As recommended by the Health Surveillance Guide (2017), the current regimen indicated and available for the treatment of LTBI is with the presentation of Isoniazid 100mg in a dosage of 5 to 10 mg/kg/day (maximum dose of 300mg/day) in 270 doses that should be taken from 9 to 12 months (BRASIL, 2017). However, from 2018, Isoniazid 300mg will also be made available to the health network, which should be incorporated by the services. In other words, there will be two presentations of Isoniazid (100mg and 300mg) in the units studied to be used in the treatment of LTBI. Studies carried out by FIOCRUZ indicate that the two formulations have bioequivalence (Daher et al, 2015).

The two presentations of Isoniazid (100mg and 300mg) will be available to be used as needed depending on the weight range of adults and children. Since overdose of Isoniazid can lead to severe drug hepatitis and death, correct use is imperative to ensure that people undergoing treatment for LTBI receive the correct dose of Isoniazid.

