# OBJECTIVE

• To analyze the occurrence of serious or unexpected adverse reactions resulting from the use of Isoniazid 300mg by the patient for the treatment of latent tuberculosis infection.

• To analyze the patient's use of Isoniazid 300mg for the treatment of latent tuberculosis infection.

• To analyze the information strategies made available to health services on the new presentation of Isoniazid 300mg for the treatment of latent tuberculosis infection.

• To analyze compliance in the prescription of Isoniazid 300mg for the treatment of latent tuberculosis infection through the Knowledge, Attitudes and Practices (CAP) strategy.

•To analyze compliance in the dispensing of Isoniazid 300mg for the treatment of latent tuberculosis infection through the Knowledge, Attitudes and Practices (CAP) strategy.

• To determine the plasma levels of patients undergoing treatment with Isoniazid 100 and 300mg

• To analyze the social representations of health professionals from the basic unit on the use of Isoniazid 300mg for the treatment of latent tuberculosis infection.

• To know the meanings of health professionals at the basic unit about the use of Isoniazid 300mg for the treatment of latent tuberculosis infection.

• To identify the role of health professionals from the basic unit in relation to patients using Isoniazid 300mg for the treatment of latent tuberculosis infection.

• To interpret how health professionals at the basic unit relate their conceptions to the prescription of Isoniazid 300mg for the treatment of latent tuberculosis infection.

• To develop and analyze the use of a computerized system for mobile devices that helps health professionals in the diagnosis and treatment process, as well as to assist in the prevention and care of people with latent Tuberculosis, evaluating its use in these health services to integrate follow-up actions as well as evaluating the degree of solvability of these actions from the system.

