Each research participant (n=36) will be invited, after reading, clarifying and signing the informed consent, to donate a blood sample at three different times of treatment (30 days of treatment; 3rd month of treatment; 6th month (at the end of ) treatment. Each plasma sample will be treated with solvent solution and filtered to prepare the specimen before performing the plasma isoniazid dosage. It will be launched in the HPLC in order to identify its chromatometric curve compared to the available isoniazid standard. In this way, it will be possible to identify the plasma level of isoniazid of participants with LTBI randomly allocated in the 100mg or 300mg arms of LTBI treatment with isoniazid in some possible subgroups: (i) patients with adequate adherence and use correctly foreseen by the Ministry da Saúde2; (ii) underdosage (those who, even with a 300mg prescription, can make a mistake and take a 100mg tablet thinking they are is receiving 300mg due to incorrect understanding or dispensing in a pharmacological presentation below the prescribed 300mg), (iii) overdose (participants who, due to a mistake in the participant's understanding, when using three 300mg tablets when it should have been 100mg); Possible drug interactions including those who are using other drugs, with any unexpected drug interactions; (iv) patients who did not correctly adhere to what was recommended and what was prescribed and informed by the prescriber even though the pharmacological presentation had been correctly dispensed.

Second stage

Study Scenario and Design

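### The two stated analysis sets fit the adverse-effect comparison badly: per-protocol removes reactions that ended treatment and tablet mix-ups, and ITT does not show reactions by tablet actually taken

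*Protocol*

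**What the plan says.** Four parts of the protocol bear on this point.

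- **Safety aim.** The first objective is "To analyze the occurrence of serious or unexpected adverse reactions resulting from the use of Isoniazid 300mg by the patient". The introduction gives the reason for care: "Since overdose of Isoniazid can lead to severe drug hepatitis and death".
- **Safety outcome.** Methods, First step: "Secondary outcomes will be evaluated by comparing adverse effects in the two groups (Isoniazid 100mg or 300mg".
- **Populations.** Analysis plan: "For the analysis of the results, two basic populations will be defined". The first is ITT, "which will include all patients regardless of protocol violations and loss to follow-up". The second is per-protocol, "including only patients who completed treatment according to the protocol criteria, excluding all violators". Both will be presented. No third set is defined for the trial.
- **Named mix-up.** The plasma subanalysis lists an overdose subgroup, put down to the participant's misunderstanding, "when using three 300mg tablets when it should have been 100mg".

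Intake and adverse effects are asked of all participants at week 2, months 1 and 2, and end of treatment (Phase 2, Follow-up). Actual use is classified only in the 36-person plasma subanalysis, and there for plasma levels.

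**The concern.** The sentence that sets up the populations covers the results in general, so the adverse-effect comparison falls under it. The reasons given for having two sets concern superiority and non-inferiority. Harm is not discussed.

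A per-protocol set is a poor base for harms because membership depends on having completed treatment. Someone whose reaction led them to stop is not a completer. Someone who took the wrong tablets is a violator. These are the people in whom a safety problem with a new presentation would show.

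ITT keeps them, but groups them by the tablet they were assigned. The first objective asks about reactions from using the 300 mg tablet. Where assignment and use differ, ITT alone does not answer that.

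At stake is the trial's stated purpose of supporting a presentation that brings no added risk for patients (Expected results).

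**Working it through.** No stated figure needs reproducing here. The check sets the two populations against the safety question and uses arithmetic only to show what can and cannot be said about size.

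**1. Who is kept, and where a reaction is counted**

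| Participant | ITT | Per-protocol |
| --- | --- | --- |
| Stops because of a reaction | Counted in allocated arm | Removed |
| 100 mg arm, takes 300 mg tablets by mistake | Counted against 100 mg | Removed |
| 300 mg arm, takes three tablets | Counted against 300 mg | Removed |

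The per-protocol column needs no assumed rate.

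**2. How much the per-protocol set removes**

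The sample size section plans on 30% abandonment with 100 mg and 19% with 300 mg. The recruitment targets give 186 + 4 × 90 = 546, or 273 per arm. Abandonment alone then removes 0.30 × 273 ≈ 82 people from the 100 mg arm and 0.19 × 273 ≈ 52 from the 300 mg arm. (The sample size section also speaks of 474 in each group; the percentages do not depend on that.) The protocol does not say how many of these would have stopped because of a reaction.

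All reactions that ended treatment are lost. As a rate, if a fraction d of an arm is removed, the whole-arm rate is (1 − d) × (rate in those kept) + d × (rate in those removed). The per-protocol rate is therefore too low whenever those removed had more reactions than those kept.

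**3. What a mix-up does to each comparison**

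Assume, for illustration only, the same adverse-effect rate b under correct use in both arms, a rate o under the mix-up, and mix-up fractions m₁₀₀ and m₃₀₀. Then

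ITT risk ratio (300 mg vs 100 mg) = [b + m₃₀₀(o − b)] / [b + m₁₀₀(o − b)].

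With b = 0.10 and o = 0.50, so o − b = 0.40:

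| Mix-ups occur in | m = 0.02 | m = 0.05 |
| --- | --- | --- |
| 100 mg arm only | 0.100/0.108 = 0.93 | 0.100/0.120 = 0.83 |
| 300 mg arm only | 0.108/0.100 = 1.08 | 0.120/0.100 = 1.20 |
| Both arms equally | 1.00 | 1.00 |
| Per-protocol, any of these | b/b = 1.00 | b/b = 1.00 |

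Over b from 0.02 to 0.10, o of 0.30 or 0.50 and m from 0.01 to 0.05, the ITT ratio runs from 0.98 down to 0.45 if all mix-ups are in the 100 mg arm. It runs from 1.02 up to 2.20 if all are in the 300 mg arm; the extreme is (0.02 + 0.05 × 0.48)/0.02 = 2.20. So ITT can move either way, while per-protocol hides the mix-up in every case.

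**4. Precision**

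For the 0.93 case with 273 per arm, expected events are 27.3 and 29.5. The standard error of the log ratio is √(1/27.3 − 1/273 + 1/29.5 − 1/273) ≈ 0.25, which gives a 95% interval of about 0.57 to 1.52. Shifts of this size lie well within sampling error.

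**5. Does the plasma subanalysis fill the gap?**

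It has 18 people per arm. The chance that a given arm's 18 include at least one mix-up is 1 − (1 − m)^18, or 17%, 30% and 60% at m = 0.01, 0.02 and 0.05. It cannot be relied on to show even one case.

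**The case against.** The strongest reply is that safety sets are usually defined in a statistical analysis plan, which is not shown here, and that naming two basic populations does not rule out a third. The populations paragraph never mentions adverse effects, and its section deals largely with treatment success and dropout. Both analyses will be presented, so anyone dropped from per-protocol still appears in ITT. Comparison by allocated arm is the natural one for a pragmatic trial.

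Much of this stands. ITT by arm is legitimate and should stay, and no participant disappears from the report altogether. A missing safety set alone would not be worth raising. But the protocol goes further than silence: it states a general rule for the results and commits to showing both sets. Applied to adverse effects, that rule yields a per-protocol comparison that leaves out the reactions of most interest. A later plan could add a set, but the stated rule would still need correcting.

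A reader might infer more: that the plan makes 300 mg look safer than 100 mg, because mix-up harm lands on the control arm. The documents do not support that. It requires mix-ups to be commoner in the 100 mg arm. The overdose subgroup is attributed to the participant's misunderstanding and linked to no arm; incorrect dispensing is mentioned under underdosage. A 300 mg participant who takes three tablets is equally consistent with the text, and ITT then charges the harm to 300 mg.

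**Conclusion.** The point holds in a limited form. The per-protocol set is unsuitable for adverse effects, and this follows from its definition. It rests on two readings: that the general sentence on populations covers the secondary outcome, and that taking the wrong tablets counts as a violation. ITT is sound as a comparison of assigned presentations but leaves the first objective, reactions from actual use, only partly answered.

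The direction and size of any distortion in the arm comparison cannot be stated. The protocol gives no adverse-effect rate and no mix-up rate, and does not place the mix-up in one arm. All the risk ratios above are illustrations. The protocol's own figures support only this: planned abandonment alone would remove 30% and 19% of the arms from the per-protocol set, for reasons it does not break down. The correction is cheap enough to make without knowing the size.

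**What to change.** Add to the analysis plan that:

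- adverse effects will be compared by allocated arm in all participants who took at least one dose, with nobody removed for stopping treatment or for a protocol violation;
- the per-protocol set will not be used for adverse effects;
- a supplementary table will give adverse effects by strength and number of tablets actually taken, with mix-ups shown by allocated arm. It should be labelled non-randomised and read beside the comparison by arm, not in place of it.

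The cost is a few sentences and one table. The strength and number of tablets taken must be recorded at the intake interviews already planned. The follow-up form is not shown, so it is not known whether it already captures them. Nothing here changes a dose or a clinical rule.
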